#### 4. Aim of the study

To evaluate the clinical performance and safety of a newly developed BIS monitoring converting device using already existing needle electrodes in patients undergoing perioperative EEG monitoring as a subject.

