#### 6. Method of participant selection

##### 6-1. Eligible patient and method of recruitment

Those who undergo surgery under intraoperative management by total intravenous anesthesia in the Department of Neurosurgery or Plastic Surgery at Kurume University Hospital

The target number of cases: 20 patients

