### 8-1. Detailed procedure

The patient will be brought into the operation room with usual medical procedure, and a commercially available BIS sensor will be attached to the forehead of the patients immediately after the introduction of anesthesia needle electrodes, and the perioperative consciousness levels and association in various BIS-related values will be compared.

- I. Before the introduction of anesthesia, both needle electrodes and a commercially available BIS sensor will be attached at the same place of the forehead
- II. Anesthesia will be introduced by propofol, remifentanyl, and rocuronium
- III. Normal anesthesia management will be done
- IV. Because the needle electrodes and the commercially available BIS sensor are at the same position, there should be no difference. The BIS monitoring system used in this study can display BIS

values from two areas, and the electrodes are attached at the same position. The homology of the EEG wave form will be observed, values calculated using EEG processing, such as SQL, SEF, Beta-ratio, and resting ratio, will be compared and recorded if there is any discrepancy and if so in which degree.

- V. After completion of the surgery, it will be recorded if there is any discrepancy and if so in which degree in increasing BIS values due to emergence.

8-2. Devices to be used (All of them are medical devices approved for clinical use)

1. NE-220B, the needle electrodes for EEG manufactured by Nihon Koden (length, 13mm; diameter 0.4mm).
2. BIS™ Complete 4 Channel Monitoring System
3. BIS™ Bilateral Sensor

8-3. Methods of allocation

This study acquires and compares information from two sensor locations in a single person. Therefore, there is no allocation.

8-4. Endpoints

Primary endpoints : BIS-related values from two different measurement locations

Secondary endpoints: perioperative complications

8-5. Analysis methods

By repeated ANOVA (post hoc test) and sequential two-group comparisons of BIS-related values, it will be proven that the observed values are the same.

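### Section 8-5 sets out to prove that the two sensors read the same by using tests of difference, which cannot show sameness and look only at means

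*Protocol*

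**What the plan says.** Protocol section 8-5 is a single sentence. It says that by repeated ANOVA, with a post hoc test, and "sequential two-group comparisons of BIS-related values, it will be proven that the observed values are the same". It is the only analysis stated for the primary endpoint, which section 8-4 gives as "Primary endpoints : BIS-related values from two different measurement locations". Neither section names an agreement statistic or an acceptable difference.

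The design is paired. Section 8-3 says: "This study acquires and compares information from two sensor locations in a single person". Step IV of section 8-1 presumes the answer: "Because the needle electrodes and the commercially available BIS sensor are at the same position, there should be no difference". The same step says that derived EEG values "will be compared and recorded if there is any discrepancy and if so in which degree", and step V asks for a similar record at emergence. No threshold is attached to either record.

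The aim in section 4 is "To evaluate the clinical performance and safety of a newly developed BIS monitoring converting device". Section 6-1 sets the size, without justification: "The target number of cases: 20 patients".

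**The concern.** There are two separate faults.

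- **The inference runs the wrong way.** ANOVA and two-group comparisons take equality of means as the null hypothesis. A non-significant result may mean that the sensors agree, or that the study was too small or too noisy to show that they do not. Read as proof of sameness, it rewards imprecision.
- **The tests address the wrong quantity.** They compare means. If the needle electrodes read high in some patients and low in others, the errors cancel and the mean difference can be zero while individual readings disagree badly. Section 3 describes BIS as a tool for judging depth of anesthesia, so agreement of the individual reading is what matters for clinical performance.

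At stake is the main conclusion of the study: that the needle and interface reading can stand in for the standard sensor. On the stated analysis that conclusion would not be valid, whatever the data showed.

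**Working it through.** **Inputs from the protocol.** 20 patients (section 6-1); paired readings (section 8-3); difference tests with sameness as the conclusion (section 8-5).

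**Inputs not in the protocol, assumed for illustration.** Two-sided alpha 0.05; SD of patient-level differences 5 to 20 BIS units; true bias 0, 5 or 10 units; equivalence margin ±5 units. The figure of 20 patients cannot be reproduced, because no inputs are given for it. What can be checked is how the stated approach behaves at that size, modelled as one paired t-test on patient-level differences.

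**Step 1: chance of missing a real bias.** The test statistic follows a noncentral t distribution with n − 1 degrees of freedom and noncentrality bias / (SD/√n). For bias 5, SD 10 and n = 20, this is 5 / (10/√20) = 2.24. With critical value 2.093 (19 df), the power is 0.565, so the result is non-significant 1 − 0.565 = 0.435, or 44%, of the time.

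Chance of a non-significant result at n = 20:

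| SD of differences | bias 0 | bias 5 | bias 10 |
|---|---|---|---|
| 5 | 95% | 1% | 0% |
| 10 | 95% | 44% | 1% |
| 15 | 95% | 71% | 19% |
| 20 | 95% | 81% | 44% |

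**Step 2: effect of study size.** For bias 5 and SD 10, the chance of a non-significant result is 86% at n = 5, 71% at n = 10, 44% at n = 20, 13% at n = 40 and 0.7% at n = 80. The smaller the study, the easier it is to conclude sameness.

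**Step 3: zero mean bias with poor agreement.** The 95% limits of agreement are bias ± 1.96 × SD. At SD 15 this is 1.96 × 15 = ±29.4 units, and at SD 20 it is ±39.2. In both cases the test is non-significant 95% of the time. These limits describe patient-level differences. Limits for single readings would be wider, because within-patient variation adds to them.

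**Step 4: the opposite error.** A consistent bias of 1 unit with SD 1 is non-significant only 1% of the time, so a precise device with a trivial offset would fail to show sameness. An equivalence test with margin ±5 accepts it about 100% of the time.

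**Step 5: a test built for the question.** Two one-sided 5% tests on the mean bias amount to requiring the 90% confidence interval to lie within the margin. With n = 20 and margin ±5, equivalence is declared with these probabilities:

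| SD | true bias 0 | true bias 5 (at the margin) |
|---|---|---|
| 5 | 99% | 5.0% |
| 8 | 71% | 5.0% |
| 10 | 39% | 4.6% |
| 15 | 3% | 0.9% |

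The incentive is now the right way round: a noisier device is less likely to pass, and a device with bias at the margin passes at most 5% of the time.

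**Step 6: precision at n = 20.** The 95% confidence interval half-width for the bias is 2.093/√20 = 0.47 SD. Each limit of agreement has standard error √(1/20 + 1.96²/38) = 0.389 SD, so its half-width is 2.093 × 0.389 = 0.81 SD. At SD 10 these are 4.7 and 8.1 units.

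**The case against.** The protocol states no alpha and never says that a non-significant result will count as sameness. That reading is inferred, though it is the only route by which the named tests could support the stated conclusion.

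The figures model one paired test, whereas section 8-5 plans ANOVA with post hoc tests and sequential comparisons of several BIS-related values. If any one significant result defeated sameness, then with zero bias and independent 5% tests the chance that all are non-significant would be 0.95^5 = 77%, 0.95^10 = 60% or 0.95^20 = 36%. So 44% and 95% are illustrative single-test figures and not properties of the full plan. This does not repair the logic: the conclusion would still rest on absence of significance, with no rule for how many tests count.

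A large bias with a small SD would be caught (bias 5, SD 5: detected 99% of the time), so a poor device could pass but need not.

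Steps IV and V of section 8-1 already record the degree of discrepancy, so the data can answer the question. This stands. The fault lies in the planned inference and not in the measurements.

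Details of an agreement analysis may properly sit in a statistical analysis plan that is not shown. That is fair, but the sentence claiming proof is fixed in the protocol itself.

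Finally, the remedy is easiest where the harm is smallest. At SD 10 the equivalence test has only 39% power, and a bound on the limits of agreement would be harder still to meet once their uncertainty is counted. This also stands, and it limits what 20 patients can be promised to show.

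**Conclusion.** The concern holds. Section 8-5 fixes tests of difference and states a conclusion that cannot follow from them. This is an error in what the protocol says and not a detail left for later. Nothing in sections 8-1 or 8-4 supplies a criterion that would rescue it.

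Under the assumptions above, a 5-unit bias at SD 10 would go undetected 44% of the time with 20 patients. Wide disagreement around a zero mean would pass a single test 95% of the time whatever the SD. The exact percentages depend on assumed SDs, biases, alpha and margin, but the direction of the fault does not. Because this is the only stated analysis of the primary endpoint, it must be corrected before the results are interpreted.

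**What to change.** Replace the sentence in section 8-5 with a paired agreement analysis:

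1. Estimate the mean bias (needle minus standard BIS) and the 95% limits of agreement, with confidence intervals, from a mixed model with patient as a random effect (Bland-Altman for repeated measures).
2. State a margin in BIS units in advance, with its justification. Claim equivalence only if the 90% confidence interval of the bias lies within the margin and the limits of agreement meet a stated bound. Say whether that bound applies to the estimated limits or to their confidence limits.
3. Remove the claim that sameness will be proven. If no margin can be justified, report agreement descriptively.

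The cost is a rewording and one pre-stated margin, plus the bound on the limits. The data and the 20 patients do not change. The price is that a positive claim becomes harder to obtain: with an illustrative ±5 margin, 20 patients give good power only if the SD is modest (99% at SD 5, 71% at SD 8, 39% at SD 10), and those figures cover the bias criterion alone. The descriptive option is feasible at 20 patients whatever the SD.

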## 9. Discontinuation criteria

At the following conditions, the study will be discontinued.

- Consent is withdrawn by patients
- Study physicians decide it inappropriate to continue the study

## 10. Correspondence to participants after conducting the study

After completing the study, we arrange participants being able to receive the best medical care (prevention, diagnosis, and treatment), obtained from the results of this study.

## **11. Expected benefits and disadvantages of participation**

### **11-1. Expected benefits by participating in this study (effect)**

Although the intraoperative anesthesia depth could be evaluated more strictly, the study subjects will not receive any direct benefit, because the study is observational, conducted within the scope of daily routine practice. Participants could contribute to future progress in medicine by providing the study results.

### **11-2. Expected disadvantages, adverse events, risks by participating in this study**

The study uses a needle electrode NE-220B for EEG, manufactured by Nihon Koden, which has been clinically used for many years (length, 13mm; diameter 0.4mm). Symptoms observed by the use of original electrodes, such as subcutaneous bleeding and infection, may occur, but the occurrence is accidental and will be extremely rare.

## **12. Protection of the participants**

### **12-1. Compliance with ethical standards**

This study will be conducted in accordance with the ethical principles of the Declaration of Helsinki and the “Ethical Principles for Medical Research Involving Human Subjects”. To conduct this study, it should be approved by the ethic committee of the University of Kurume.

### **12-2. Methods for protecting personal information**

Investigators being involved in the study execution take protection of privacy and personal information of participants well in consideration. The principal investigator will establish the necessary system to protect data and other information when conducting the study. If the data obtained in this study will be used for other purposes than this study, another consent will be obtained from the patient as necessary.

## **13. Consent of patients (informed consent)**

Before perioperative period, consent will be obtained from the participants after explaining about the study. A withdrawal form will be handed out, and if the patient withdraws the consent by giving the withdrawal form or explaining verbally before the anesthesia introduction, the patient will be excluded from the study.

**14. Costs burden to participants and compensation for loss**

**14-1. Costs burden**

The study will be conducted within the scope of daily routine practice and the coverage of patient's health insurance. Therefore, observation, investigations, and used medications will be covered by the patient using the health insurance. The cost required for the use of needle electrodes and the newly developed BIS monitoring will be covered by the Department of Anesthesiology and there will be no additional cost for patients.

**14-2. Loss compensation for health hazards**

If health hazards occur due to this study, in principle, the treatment will be covered by the health insurance of the participant, and proper treatment and necessary measures will be taken. Because the cost will be borne by the patient, there will be no monetary compensation from the study institution.

**15. Management and disposal methods for specimens and information (data)**

Data regarding this study will be anonymized in a linkable fashion and be stored on a computer that belongs to the Department of Anesthesiology and is not connected to the internet. The signed consent forms and other forms will be stored in locked cabinets in the Department of Anesthesiology. Storage period is for five years. All documents related to the study except medical information will be shredded and disposed.

**16. Funding source and conflict of interest**

This study will be carried out using the internal research budget of the Department of Anesthesiology and will not be funded by external companies. Therefore, there is no conflict of interest.

**17. Property of the results (patent)**

Newly generated intellectual properties from this study will belong to the University of Kurume.

**18. Disclosure of the study information and results**

The results generated from the study will be presented at academic meetings of the Japanese Society of Anesthesiologists and the American Society of Anesthesiologists, and will be published in an academic journal.

**19. Secondary use of data (ancillary studies)**

It is possible to conduct ancillary studies using the data (specimens and information) from the study. In that case, the specimens and data will be anonymized and privacy will be protected. To conduct an ancillary study, the data will be used after a new study protocol is reviewed and approved by the ethic committee.

